## Methods: participants, interventions and outcomes

### Participants

### Study setting {9}

Study participants are selected and included by associate investigators in their respective centers located in several cities in France. The list of investigators is kept at the Fondation LENVAL Pediatric Hospitals of Nice CHU-Lenval, Delegation for Clinical Research and Innovation (DCRI) of Nice University Hospital Center, and can be requested from the clinical research associate.

### Eligibility criteria {10}

#### Criteria for inclusion

Age ≥ 8 years old and ≤ 13 years old.Diagnosis of a specific neurodevelopmental reading disorder, according to DSM-5 criteria, with scores ≤ − 1.5 standard deviation from the mean on leximetric tests: Alouette [113, 114], Evaléo 6–15© [115] or Evalec© [116].Phonological deficit: Scores in speed or accuracy lower than 1.5 SD from the mean for phonemic analysis tasks or non-word repetition tasks or automatized quick naming tasks of the Evalec Battery.Visual-attentional deficit: Scores in speed or accuracy lower than 1.5 SD from the average for global or partial reporting tasks of the Evadys© test [117] or for attentional focus tasks of the Sigl© test [118].All children have both at least one phonological deficit and at least one visual-attentional deficit.Family home equipped with a connected computer set up for daily training sessions.Informed consent signed by both parents or by a representative of parental authority.

#### Criteria for non-inclusion

Intellectual retardation, neurological disorders, pervasive developmental disorder (DSM-5).Primary sensory deficit.Educational deficiencies, that refer to inadequate schooling (e.g., prolonged or repeated absences from school) or inappropriate teaching (e.g., a teacher who does not follow national guidelines for reading instruction).Attention-Deficit Hyperactivity Disorder (ADHD), Specific Language Impairment (SLI).Prior intensive daily phonological or visual-attentional training.

#### Exclusion criteria (or study exit criteria)

Participants are temporarily or permanently excluded from the study if:They interrupt daily training for more than a continuous period of 15 days without a valid reason determined at the investigator’s discretion.They do not participate regularly in daily training, as left to the investigator’s appreciation.The participants or their parents withdraw their consent.

The interruption may occur after consent has been obtained or after randomization. A child who wishes to withdraw consent may tell his/her parents or the speech-language pathologist who will inform the principal investigator. Parents may also inform the principal investigator directly (contact information is available at the end of the information sheet that goes with the consent form). For, all patients, the speech-language pathologist must send a patient identification form to the principal investigator indicating the date the consent was signed, the date of randomization, the randomization group, and, if applicable, the date of discharge from the trial.

### Who will take informed consent? {26a}

Oral and written information is given to the parents and the child. Consent form signed by both parents or by legal guardians is taken by each investigator at the site of inclusion.

### Additional consent provisions for collection and use of participant data and biological specimens {26b}

The processing of data complies with the French Data Protection Act No. 78–17 of January 6, 1978 as amended and Regulation (EU) 2016/679 of the European Parliament and of the Council of April 27, 2016 applicable as of May 25, 2018 (General Regulation on Data Protection, RGPD).Data is collected and used in accordance with the reference methodology for processing personal data in the context of health research requiring the express or written consent of the person concerned (MR-001) and has been declared to the CNIL (deliberation no. 2018–153 of May 3, 2018).

## Interventions

### Explanation for the choice of comparators {6b}

#### Main evaluation criteria

Reading efficiency is measured at inclusion (Test 1), at the end of phase 1 without intensive training (Test 2), at the end of the three training periods of phase 2 (Test 5) and after phase 3, i.e., 2 months after the training has stopped (Test 6) by five reading tests:Alouette©, a widely used standardized French reading test, measures speed and accuracy when reading a meaningless text and provides a reading age [113] and both speed and accuracy scores [114].DeltaText© measures speed and accuracy of meaningless texts matched in number of words, length and complexity [119].Mouette-Pingouin© measures the speed and accuracy of word identification of meaningful texts matched in length and complexity to control for a test/re-test effect using two texts controlled for word number and word frequency [115].Eval2M© measures the speed and accuracy of identification of words presented in columns [115].Evalec© measures the respective speed and accuracy of identification of regular words, irregular words and pseudowords [116].

#### Secondary evaluation criteria

Related to the secondary objectives:Reading efficiency after the phonology training and after visual-attentional training will be measured by the five reading tests in Test 3 for the two groups (G1: PHO/VA/CM, G2: VA/PHO/CM).Reading efficiency after the two phonological and visual-attentional training periods conducted in a different chronological order in each group, will be measured by the five reading tests in T4 for the two groups.Spelling skills will be measured by Chronosdictées© [120] which proposes two versions with sentences matched in length, lexical frequency and phonetic complexity.Reading comprehension will be measured by the closure test ORLEC L3© [121, 122].Reading disorder impact (reading interest, academic performance and self-esteem) will be measured by two questionnaires completed by each child and his or her parents, in which they express their degree of agreement or disagreement.

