**Methods:**

This multicenter randomized crossover study will be conducted in three phases and will involve 120 dyslexic children between the ages of 8 and 13 years. The first phase serves as within-subject baseline period that lasts for 2 months. In this phase, all children undergo weekly speech-language therapy sessions without additional training at home (business-as-usual). During the second phase, all dyslexics receive three types of intensive interventions that last 2 month each: Phonological, visual-attentional, and cross-modal. The order of the first two interventions (phonological and visual-attentional) is swapped in two randomly assigned groups of 60 dyslexics each. This allows one to test the efficacy and additivity of each intervention (against baseline) and find out whether the order of delivery matters. During the third phase, the follow-up period, the intensive interventions are stopped, and all dyslexics will be tested after 2 months. Implementation fidelity will be assessed from the user data of the computerized intervention program and an “intention-to-treat” analysis will be performed on the children who quit the trial before the end.

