### Secondary objectives

Assess the efficiency of each intervention against baseline.Assess the efficiency of each intervention as a function of the severity of the “underlying cognitive deficits”.Assess the effects of intensive intervention (phase 2) compared to baseline (phase 1) on reading interest, academic performance, and self-esteem.Assess the stability of the intervention effects in all of the above measures 2 months after training.

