### Secondary hypotheses

*Hypothesis 1*: Intensive phonological or visual-attentional training is more effective than conventional non-intensive and non-specific therapy*Hypothesis 2*: Intensive, specific, multimodal training (test 5) significantly improves reading interest, academic performance, and self-esteem compared to conventional non-intensive therapy (test 2).*Hypothesis 4*: These intervention benefits should last 2 months later (test 6).*Hypothesis 5*: No significant difference as for the effects on reading skills is expected between phonological versus visual-attentional training (test 3).

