### Statistical analysis

To assess the gains for each dependent variable (reading, spelling and reading comprehension scores) in each group (1 and 2) and for the total sample, we will calculate the means difference and confidence intervals between T1 and T2 (Phase 1 without training), between T2 and T4 (Phase 2 after 16 weeks of training), between T4 and T5 (Phase 2 after 24 weeks of training), and between T5 and T6 (Phase 3 after 8 weeks without training).The gains between T1 and T2 will be compared with the gains between T2 and T4, between T4 and T5, and between T5 and T6 to determine whether the T2T4, T4T5, and T5T6 differences represent a significantly greater gain compared to the no training phase (T1T2).

To measure the effect of each type of training, we will calculate the effect size, *Cohen’s d* or *η*^*2*^, from the gains of each dependent variable. Cohen’s d scores of 0.3, 0.5 and 0.8 are considered to represent small, medium and large effect sizes, respectively.3.To determine whether the order of PHO/VA versus VA/PHO training leads to different effects, we will perform a repeated Anova with cross-over between groups to compare the gains between T2 and T4 of each group, controlling for gains between T2 and T1 without training. This analysis will also allow us to determine if there is a significant difference between the effects of 8 weeks of phonological training and 8 weeks of visual-attentional training between T2 and T3.4.Exploratory factor analysis will verify that all the items in the questionnaires (pre-test and post-test Likert scale) or, failing that, some of them can be combined into a score. If necessary, the composite scores will be analyzed as continuous variables. If not, graphical representations in the form of histograms will be used to visualize the variations, and χ^**2**^ tests will be carried out.

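### Phonological and visual-attentional training are to be judged one by one against baseline, but the listed gains give only their sum, and the T3-T4 gain enters no per-training estimate

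*Protocol article*

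**What the plan says.** Trial design {8} gives all children both trainings, with the order swapped between two groups of 60: G1 has phonological then visual-attentional training, G2 the reverse, and cross-modal training follows in both.

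- **Aim.** Secondary objectives: "Assess the efficiency of each intervention against baseline". The Abstract says the swapped order allows one to "test the efficacy and additivity of each intervention (against baseline"). Hypothesis 1 likewise sets phonological or visual-attentional training against conventional therapy.
- **Measurement.** Secondary evaluation criteria: "Reading efficiency after the phonology training and after visual-attentional training will be measured by the five reading tests in Test 3". The next criterion, "Reading efficiency after the two phonological and visual-attentional training periods conducted in a different chronological order in each group", is read at T4 and concerns the two trainings together.
- **Gains to be compared with T1-T2.** Statistical analysis lists the gains "between T2 and T4 (Phase 2 after 16 weeks of training), between T4 and T5 (Phase 2 after 24 weeks of training"), and T5-T6.
- **Order.** The same section says "we will perform a repeated Anova with cross-over between groups to compare the gains between T2 and T4 of each group", controlling for the T1-T2 gain. It adds that this analysis will also compare the two trainings over T2-T3.
- **Phonological versus visual-attentional.** In Hypothesis 5, no significant difference "is expected between phonological versus visual-attentional training (test 3").

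**The concern.** Of the three trainings, only cross-modal has its own interval (T4-T5) among the gains compared with baseline. T2-T4 contains both other trainings in both groups, so it cannot separate them. T2-T3 appears only in the comparison between the two trainings, and T3-T4 is named nowhere.

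Two stated aims are therefore not met by the analysis as written. The effect of phonological or visual-attentional training against baseline has no listed contrast. Additivity asks what the second training adds after the first, which is the T3-T4 gain. If a reader supplies the missing contrast from Test 3 alone, each training is judged in 60 of the 120 children and only when given first, although the other 60 are measured before and after the same training at T3 and T4.

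**Working it through.** **Plan's own figure.** Sample size {14} gives 55 per group for d = 0.700. Power is not stated. A two-sample t-test at two-sided 5% needs 54.02, so 55, at 95% power. With 10% dropout, 110/0.9 = 122.2, so 123, close to the stated 120. This gives the 60 per group used below and does not otherwise bear on the point.

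**Intervals by group**

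| Interval | G1 | G2 | Compared with T1-T2? |
|---|---|---|---|
| T1-T2 | usual therapy | usual therapy | reference |
| T2-T3 | phonological | visual-attentional | not listed |
| T3-T4 | visual-attentional | phonological | not listed |
| T2-T4 | both | both | yes |
| T4-T5 | cross-modal | cross-modal | yes |

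**Assumptions (not in the article).** 60 per group, score SD 1, independent test errors with variance e = 1 - r, r between 0.80 and 0.95, linear child-specific progress with slope SD s, no period effect and no carry-over. Examples use r = 0.90, so e = 0.10, unless stated.

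**1. Each training against T1-T2**

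- First position: Var[(T3-T2) - (T2-T1)] = 6e. In one group, SE = sqrt(6e/60) = sqrt(0.6/60) = 0.100.
- Second position: Var[(T4-T3) - (T2-T1)] = 4e.
- Average of the two positions, from different groups: SE = sqrt((6e + 4e)/60/4) = sqrt(1.0/240) = 0.065.
- Ratio 0.645, a reduction of about 35%, the same for every r.

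Part of this comes from using all 120 children's baseline gain. If the first-position estimate is instead the mean T2-T3 gain of one group minus the mean T1-T2 gain of all 120, then with s = 0 its variance is 2e/60 + 2e/120 + e/60 = 4e/60 (the last term arises because T2 is shared). SE = sqrt(0.4/60) = 0.082. The ratio is sqrt(10/16) = 0.79, a reduction of about 20%.

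**2. Phonological versus visual-attentional**

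- Unadjusted T2-T3 gain, s = 0: SE = sqrt(2 × 2e/60) = 0.082.
- Adjusted for the T1-T2 gain, as the plan states: residual variance 2e - e²/(2e) = 1.5e, so SE = sqrt(3e/60) = 0.071.
- Crossover, using T2-T3 and T3-T4: SE = sqrt(12e/60)/2 = 0.071.

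Without slope variation the crossover saves nothing over the adjusted comparison. With slope variation the adjusted residual variance is (2e + s²) - (s² - e)²/(2e + s²):

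- r = 0.90, s = 0.1: 0.21 - 0.0081/0.21 = 0.1714, SE = sqrt(2 × 0.1714/60) = 0.0756, against 0.0707 for the crossover. Saving about 7%.
- r = 0.95, s = 0.2: 0.14 - 0.0001/0.14 = 0.1393, SE = 0.068, against sqrt(12 × 0.05/60)/2 = 0.050. Saving about 27%.

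**3. Which model can give the against-baseline contrasts.** Take gains over T1-T2, T2-T3 and T3-T4, with a free term for each of the three periods plus one for each training. In both groups the two training indicators sum to the indicators of the second and third periods, so the five columns have rank 4. The difference between the trainings is identifiable; each training against no training is not. Any contrast with T1-T2 therefore has to assume no period or practice trend.

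**The case against.** The strongest objection is that Test 3 is a sound place to compare the two trainings. The text fixes it consistently. Hypothesis 4 expects benefits to last, no washout is described, and the Background reports that one visual-attentional program also improves phonemic awareness, so carry-over into T3-T4 is plausible. With the planned adjustment for T1-T2, Test 3 also loses little or no precision except where children's rates of progress vary markedly. This stands: for phonological versus visual-attentional training the plan's choice is defensible.

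A reader might infer that half the data are thrown away, or that the trial is analysed simply as a first-period parallel comparison. The article does not support that: T4 enters the T2-T4 gain and the order test. What is unused is the T3-T4 gain for per-training estimates.

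It can also be said that the repeated-measures crossover ANOVA, or the promised effect size for each type of training, might cover T3-T4, or that an analysis plan would settle it. But the ANOVA is aimed at T2-T4 between groups, the effect sizes are to come from gains of which none listed isolates either training, and the article is not silent: it names its intervals and time points. That part of the objection does not remove the gap.

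**Conclusion.** The point holds for the against-baseline aim. As written, the analysis does not give the effect of phonological or visual-attentional training against baseline, nor what the second training adds, although T3 and T4 are measured in all children. Using both positions would reduce the standard error of each training's contrast with T1-T2 by about 35%, or about 20% against a first-position estimate that already uses all 120 baseline gains. Both figures rest on independent test errors, linear progress, no period trend and no carry-over; none of these can be checked from the article.

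The point does not extend to a serious loss of precision for phonological versus visual-attentional training, where the saving is about zero without slope variation, about 7% at r = 0.90 with slope SD 0.1, and 27% only at r = 0.95 with slope SD 0.2. It concerns secondary objectives and leaves the main comparison of the combined intervention untouched.

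**What to change.** 1. For each training, report the gain minus the T1-T2 gain by position: phonological from G1 T2-T3 and G2 T3-T4; visual-attentional from G2 T2-T3 and G1 T3-T4. Then report the average of the two positions.
2. Take these from one repeated-measures model on T1 to T4 with group-by-time means and a child effect. Do not combine free period terms with both training terms for these contrasts. State that any contrast with T1-T2 assumes no period or practice trend.
3. Keep the between-group T2-T3 comparison, adjusted for the T1-T2 gain, as the main test of phonological versus visual-attentional training, because it is free of carry-over. Give the crossover estimate as supporting.

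The cost is analysis wording; no new assessment is needed. The downside is small: the averaged estimate mixes first and second position and assumes that carry-over is small, which is why the by-position estimates should be shown beside it.

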### Intervention description {11a}

Each intervention lasts 8 weeks, 15 minutes a day, 5 days a week and combines training for an underlying cognitive deficit (UCD) with training of a reading process. Phonological and visual-attentional UCD trainings are associated with word reading and spelling tasks. Cross-modal training is associated with text reading tasks. Within the phonological and the visual-attentional training periods, the precise nature of the training exercises is determined by the individual profile according to the initial evaluation related to Test 1. Cross-modal training is the same for all participants but is adapted to the reading level of each child.

#### Description of phonological training

Training can focus on three underlying phonological cognitive processes: Categorical perception (CP), phonological serial memory (PSM) and rapid automatized naming (RAN). Training only targets the participant’s most deficient phonological processes according to phonological tests in Test 1 and to baselines measured at the beginning of each training (CP, PSM, RAN). Thus, training for each phonological UCD varies as a function of the nature and intensity of each child’s disorder. For example, training may target CP and phonics instruction in the first month and focus on PSM and phonics instruction in the second month for children without RAN deficit. Phonological cognitive deficits training (CP and/or PSM and/or RAN) is always associated with phonics instruction training.

##### Categorical perception training: *RapDys*©

The intervention is implemented on a computerized device using RapDys© software [123]. It aims at modifying an allophonic mode of perception, i.e., an over-discrimination of infraphonemic acoustic differences, into a categorical or phonemic mode of perception. The child learns to discriminate and/or identify increasingly fine acoustic differences between two different phonemes. The Voice Onset Time (VOT) changes from allophonic peaks at +/− 75 ms VOT to phonemic peaks at +/− 5 ms VOT.

The child’s allophonic discrimination skills are assessed by a discrimination task and a syllable identification task (/də/ and /tə/) provided by the software. Depending on the child’s initial performance and response to training, the software progressively reduces the acoustic distance between two phonemes around the phonemic voicing boundary. Training consists in presenting the syllables /də/ and /tə/ on a VOT continuum whose values vary between − 75 and + 75 ms. The frequency transitions F1, F2, and F3 are 200, 2200, and 3100 Hz respectively, and the equilibrium position is 500, 1500, and 2500 Hz respectively. The frequency F0 is constant at 120 Hz. Each syllable of the continuum lasts 200 ms. When the child obtains a score of correct responses in discrimination or syllable identification that stabilizes above 75%, the next step is implemented.

##### Phonological serial memory training: *PhonopidoW*©

When the child’s score on the non-word repetition subtest indicates deficient performance of phonological short-term memory [116], training with PhonopidoW© software [124] is proposed. This intervention consists in exercises that require discriminating one sound among a sequence of several sounds, comparing or composing sequences of sounds. Contrary to the categorical perception task, the trained phonemes do not present any frequency variations. The phonological proximity between the sounds and the phonological memory load can be parameterized. Each syllable heard is simultaneously associated with a written presentation of the phoneme. Thus, this software also aims at strengthening the grapho-phonological conversion process. The clinician can remotely recommend the specific exercises to be performed.

##### Rapid automatized naming training: *naming speed*©

If the score of the RAN subtest is pathological [116], the digital Naming Speed program inspired by the Italian Run the RAN program [40] is proposed to the child. This program was created specifically for this study since there is no equivalent in French. This computerized intervention trains children to name more rapidly non-alphanumeric visual stimuli and consequently trains the different cognitive processes involved in reading such as left-to-right visual scanning, visual processing complexity, visual attention, lexical access and phonological planning. Five images of black and white objects from the LEAD lexicon database [125] are presented on the screen and randomly repeated on horizontal lines in matrices of 20 to 60 stimuli (see Fig. 3). The child names the images, in the reading direction, keeping the naming speed provided automatically by a red cursor around the image to be named. As the training progresses, the naming speed is increased from a single image to 2, 3, 4 and 5 images to be named simultaneously. The required naming speed increases as the red cursor duration per stimulus decreases from 200 ms to 50 ms. The distance and lexical frequency of the stimuli progressively decrease at the same time as the phonological complexity and the number of stimuli increase. The training is completed when the child reaches the naming speed expected for his or her age, according to the French standards of the Evalec© [116] and La BALE tests [126].

